### 3. Introduction

Psoriatic arthritis (PsA) is a chronic systemic immune mediated inflammatory disease characterized by the association of arthritis and periarticular inflammation with skin psoriasis. PsA is regularly allied with plaque psoriasis and presents as asymmetric mono-/oligoarthritis or symmetric polyarthritis, distal interphalangeal (DIP) joint involvement and/or axial disease. Other common PsA features are enthesitis, dactylitis and psoriatic nail dystrophy (1-6).

PsA occurs in around 30% of patients with psoriasis, while its population prevalence estimates range from 0.1-0.5% worldwide (7, 8). Typically, psoriasis precedes the development of arthritic symptoms by several years (9, 10). However, the clinical patterns of PsA are heterogeneous and may vary in an individual patient over time, which renders recognition of the disease by non-rheumatologists and patients challenging (6, 11, 12).

The medical and economic burden of PsA could be significant for the patient and society. Up to 30% of PsA patients exhibit a progressive, disabling form of arthritis and almost 70% of PsA patients seen in clinics have evidence of erosive disease (2, 3, 11, 12). PsA may thus lead to impaired physical function, decreased quality of life, work disability, and is also associated with certain comorbidities.

Initially, the recognition of comorbidities has been limited to the classical features or extra-articular manifestations (EAMs) of spondyloarthritis, such as inflammatory bowel disease and uveitis (5, 11, 13-15). Over the past few years, it has been increasingly recognized that an increased prevalence of both novel and traditional cardiovascular risk factors as well as of established cardiovascular disease, such as ischaemic heart disease and cerebrovascular disease, represents a major source of morbidity and mortality in PsA (16-18). The burden of cardiovascular disease is larger in PsA than in psoriasis itself and may be reduced by systemic anti-inflammatory treatment (19, 20). Further, obesity, metabolic syndrome and type II diabetes mellitus, which occur frequently in PsA patients, may negatively affect disease activity and response to therapy (21-23). Of note, increased incidence rates of malignancies other than skin cancer, and similar to that in patients with rheumatoid arthritis, were found in the North American CORRONA database (24).

To improve long-term outcomes in patients with PsA, early and appropriate treatment seems to be important, starting with timely diagnosis. It has been shown that patients with more than a 6-month delay only in rheumatology consultation had more structural damage and worse physical function than those who visited a rheumatologist within 6 months of symptom onset (25). This observation is supported by two former studies: a delay in PsA diagnosis for more than 1 year was associated with worse physical function (26), and patients seen within the first 2 years of PsA had clinically less severe disease and less radiographic progression than those who presented themselves 2 years after symptom onset (27).

Effective treatment of PsA should generally consist of disease modifying antirheumatic drugs (DMARDs), first conventional systemic DMARDs (csDMARDs), followed by biologic DMARDs (bDMARDs) (28-30). There is however lack of evidence that csDMARDs inhibit radiographic progression in PsA. Also a direct proof that early versus delayed treatment with csDMARDs is beneficial in the long-term is missing in PsA (31). Concerning bDMARDs, it has been shown that patients who received an anti-tumor necrosis factor agent (anti-TNF) within 2 years of PsA duration experienced greater improvements in arthritis scores and patient reported outcomes (PROs) than those with more than 2 years of PsA (32). Further, the first randomized controlled trial in spondyloarthritis (TICOPA) that compared a treat to target approach with standard of care in early PsA patients demonstrated significantly improved joint and skin outcomes by the tight disease control approach.

Confidential Information

No use or disclosure outside AbbVie is permitted without prior written authorization from AbbVie

That consisted of targeting minimal disease activity (MDA) and stepwise treatment algorithm starting with methotrexate as the first cdDMARD and treatment escalation every 3 months if the target of MDA was not achieved. At the end of the TICOPA trial, 37% of patients were on a bDMARD in the tight control arm versus 7.6% only in the standard care arm (33).

A number of international and national recommendations for the management of PsA and corresponding treatment algorithms have been published in the past few years in both rheumatology and dermatology (28-31, 34, 35). Ideally, management of PsA should address joints and skin as well as extra-articular manifestations and comorbidities (34, 35). It has been demonstrated that PsA patients receiving a multidisciplinary care, involving both rheumatologists and dermatologists in a US clinic, were more likely to receive systemic medication (25% vs 15%) and be treated with a biologic agent (37% vs 16%) than in prior unidisciplinary care (36).

While consensus is evident among the recommendations on the main treatment principles, the extent to which they are followed by practicing physicians is unknown. In reality it appears that many patients with PsA are not diagnosed, or are undertreated or not treated systematically (34, 37). A recent large population based multinational survey conducted in North America and Europe revealed that approximately 15% of patients with PsA had not seen a health care provider in the past year, and almost 60% were not being treated for their joint disease (38).

## 4. Rationale

Evidence suggests that timely and effective management can improve long-term outcomes in patients with PsA. The factors influencing management decisions in PsA are not well understood. In the field of diabetes mellitus, the interactions of patient, physician and systemic factors were found to have implications for the implementation of a diabetes management model (39).

Early diagnosis of PsA is the first and crucial step in effective management of PsA, The detection of inflammatory musculoskeletal symptoms drives PsA diagnosis. The clinical patterns of PsA are heterogeneous and may vary in an individual patient over time, which renders recognition of the disease by non-rheumatologists and patients challenging, leading to a delay in diagnosis and worse long term outcomes. Therefore, the time of musculoskeletal symptoms onset is selected in this study as the anchor date for describing different management steps in patients with PsA. In order to assess this aspect in the overall PsA population both patients with established and suspected PsA diagnosis will be asked to participate in the study. Medical care of PsA patients are provided by various clinical specialties, such as rheumatologists, dermatologists, other specialists and primary care practices. In order to describe the overall PsA population, which includes patients with mild disease that are not consulting physicians with rheumatology or dermatology expertise, the study aims to include PsA patients from all specialties providing medical care.

This study is expected to provide important insights into the factors influencing management of PsA, which may aid planning improvements in the standards of care in this chronic systemic disease.

## 5. Study Objectives

### Primary objective:

- To evaluate the association between the clinical specialty setting and time from inflammatory musculoskeletal symptom onset to PsA diagnose and to different management steps in patients with a confirmed PsA diagnosis

### Secondary objectives:

- To explore the association between the timing of various management steps and current disease activity and burden in patients with a confirmed PsA diagnosis
- To describe the disease characteristics and comorbidities of patients whose suspected PsA diagnosis is not confirmed through a current routine rheumatological and dermatological assessment

This is an observational study. It is not designed to identify or quantify a safety hazard relating to an authorized medicinal product.

## 6. Observational Plan

### 6.1. Study Conduct

This study will be performed in a cross-sectional, observational, multi-country, multi-center format in approximately 15 countries across different geographical regions.

The study population will consist of patients who are 18 years or older, have been diagnosed with suspected or established Psoriatic Arthritis (PsA) and attending a routine clinical visit at the participating clinical sites. Suspected PsA diagnosis is based on clinical judgement of the recruiting physician.

In order to describe the overall PsA population, all specialties providing medical care of PsA patients will be included. The study will be conducted in a convenience sample recruited at rheumatology, dermatology, other specialist and primary care practices. These are providing medical care for 37-38% (rheumatology), 22-28% (dermatology), 7-12% (other specialists) and 28% (primary care practices) of PsA patients, respectively, depending on the country (38). Other specialties may include orthopedists, ophthalmologists, physiatrists and podiatrists according to the standard practice in the respective country (34). For the sake of convenience, other specialist and primary care practices will be referred to as non-rheum/non-derm sites in this research plan.

Patients with a suspected or an established diagnosis of PsA scheduled for routine visit at the recruiting site (dermatologist, rheumatologist or a non-rheum/non-derm site) can be offered the opportunity to participate in the study. Patients will be recruited on a consecutive basis. Patient characteristics, relevant co-morbidities and medical history, disease, diagnostic and treatment data will be documented in the Data Recording Form (DRFs) for data available in the medical charts.

For the management of PsA patients a regular collaboration between different specialties is advised by established clinical recommendations (28-31, 34, 35). In order to ensure most accurate and standardized assessments of joint and skin scores as recommended in guidelines (29), the recruiting site will advise a consulting visit with a dermatologist and/or a rheumatologist for a routine PsA disease assessment. The consulting visit for a patient recruited at a rheumatology site will be with a dermatologist, for a patient recruited at a dermatology site, the consulting visit will be with a rheumatologist. Patients recruited at non-derm/non-rheum sites will be advised for consulting visits with a dermatologist and a rheumatologist, depending on country practice, based on the respective specialty assessments specified in DRF module 2 and module 3.

Consulting visits for current PsA disease assessments by dermatologist and/or rheumatologists usually happens between a 12 weeks period after a routine visit at the recruiting site and will be documented in the Data Recording Forms (see Figure 1). Treatment, procedures and diagnostic methods will follow physicians' routine clinical practice.

Validated patient questionnaires will be used to evaluate the current disease activity and burden. No patient identifiable information will be captured.

To assess the generalizability of the data enrolled, the physician will be asked to document on a separate Data Reporting Form (DRFs) the number of patients who are eligible but refuse to participate in the study. Only age ranges (<30 years, 30-45 years, > 45 years) and reason(s) for not participating (no time, not interested, does not speak the language of the questionnaires provided) will be collected.

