## 8. Data Analysis Plan

### 8.1. Endpoints

#### Primary Endpoints

- Time from inflammatory musculoskeletal symptom onset to PsA diagnosis
- Time from PsA diagnosis to first csDMARD
- Time from PsA diagnosis to first bDMARD
- Time from first csDMARD to first bDMARD

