### 8.3. Sample Size Calculation

The factor that is most likely to influence the PsA management components of interest is clinical specialty. However, there is no scientific basis currently to judge the effect size.

So this will be an exploratory study and objectives are exploratory in nature (non-confirmatory) and no adjustment for multiplicity will be made.

With 400 evaluable patients in rheum and dermatology sites, the study has 90% power to detect a difference in means between the two specialties with a two-sample t-test at a significance level of 5% assuming an effect size of 0.229. With 400 evaluable patients in rheum or dermatology sites and 200 evaluable patients in non-rheum/non-dermatology sites, the study has 90% power to detect a difference in means between rheum vs. non-rheum/non-dermatology or dermatology vs. non-rheum/non-dermatology, respectively, with a two-sample t-test at a significance level of 5% assuming an effect size of 0.281.

The estimated drop-out rates due to non-confirmed PsA diagnosis are 10% in rheum, 15% in dermatology and 25% in non-rheum/non-dermatology sites. Hence, a total number of approximately 1200 patients (450:480:270 in rheum:dermatology:non-dermatology/non-rheum, respectively) has to be recruited in order to achieve 1000 evaluable patients (400:400:200 in rheum:dermatology:non-dermatology/non-rheum, respectively).

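### Patients whose PsA is confirmed at a consult the study prompts are pooled with patients diagnosed before recruitment, and the prompting differs by specialty, the exposure under study

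*Protocol*

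**What the plan says.** - **Who enters.** Sections 4, 6.1 and 6.1.1 admit patients with suspected or established PsA. On the former, section 6.1 says: "Suspected PsA diagnosis is based on clinical judgement of the recruiting physician".
- **The consult.** Section 6.1 says that "the recruiting site will advise a consulting visit with a dermatologist and/or a rheumatologist for a routine PsA disease assessment", and gives accurate, standardized joint and skin scores as the reason. Rheumatology-site patients are referred to a dermatologist. At dermatology sites, "for a patient recruited at a dermatology site, the consulting visit will be with a rheumatologist". For the remaining settings (called other sites below): "Patients recruited at non-derm/non-rheum sites will be advised for consulting visits with a dermatologist and a rheumatologist, depending on country practice".
- **Confirmation.** The secondary objectives in section 5 treat the current rheumatological and dermatological assessment as the point where a suspected diagnosis is or is not confirmed. Table 1 ticks confirmation of PsA for the recruiting site, the rheumatologist and the dermatologist, and ticks PsA treatment for the recruiting site only.
- **Analysis.** The first primary endpoint in section 8.1 is "Time from inflammatory musculoskeletal symptom onset to PsA diagnosis". Two others start at PsA diagnosis and end at the first csDMARD or bDMARD. Section 8.2 limits the analysis to confirmed patients, specifies linear or logistic models, and reuses these times as explanatory variables for disease activity and burden. It does not distinguish diagnosis before recruitment from confirmation during the study.
- **Rates.** Section 8.3: "The estimated drop-out rates due to non-confirmed PsA diagnosis are 10% in rheum, 15% in dermatology and 25% in non-rheum/non-dermatology sites".

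**The concern.** The primary objective relates clinical specialty to delay in diagnosis and treatment. For a patient who is only suspected at recruitment, that delay is still running. The study then advises a visit that can end it, and the resulting confirmation makes the patient eligible for the primary analysis. A routine-care interval and an interval ended by study conduct are different quantities, yet they would be averaged together.

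The mixture need not be the same in each setting. A rheumatology site needs no prompting to obtain a rheumatologist's opinion. A dermatology-site patient is referred to a rheumatologist, and an other-site patient to both specialists, depending on country practice. Prompting therefore varies with the exposure.

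The diagnosis-anchored DMARD endpoints have a second difficulty. Treatment is recorded at the recruiting site. If the diagnosis is dated at a later consult, any DMARD already recorded precedes it, giving a zero or negative interval. A DMARD started because of the new diagnosis has almost no time to be observed.

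**Working it through.** **1. The plan's own figures.** Two-sided 5%, two-sample t-test, SD 1: 400 vs 400 at effect size 0.229 gives 89.9% power, and 400 vs 200 at 0.281 gives 90.0%. Recruitment: 400/0.90 = 445, 400/0.85 = 471, 200/0.75 = 267, total 1183. The plan rounds up to 450, 480 and 270 (1200). The sample size arithmetic is sound. What matters here is who the evaluable patients are.

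**2. Inputs.** From section 8.3, the non-confirmed share of recruits is u = 0.10 (rheumatology), 0.15 (dermatology), 0.25 (other). The protocol does not give the share of suspected patients who are confirmed (c), the suspected share of recruits (f), or the mean change in delay among newly confirmed patients (t, in SD units). All three are assumed below. It is also assumed that only suspected patients can be non-confirmed.

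**3. Equal confirmation rate c in every setting.** The suspected share is f = u/(1 − c), and the newly confirmed share of evaluable patients is s = f·c/(1 − u).

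| c | f: rheum / derm / other | s: rheum / derm / other |
|---|---|---|
| 0.25 | 13.3% / 20.0% / 33.3% | 3.7% / 5.9% / 11.1% |
| 0.50 | 20.0% / 30.0% / 50.0% | 11.1% / 17.6% / 33.3% |
| 0.75 (limit) | 40% / 60% / 100% | 33% / 53% / 100% |

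The last row is the limit because every other-site recruit would be a suspected case. In each row s is 3 times as large in other sites as in rheumatology, since (0.25/0.75)/(0.10/0.90) = 3.

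**4. Equal suspected share instead, f = 0.40 (assumed).** Newly confirmed patients are f − u of recruits: 0.30, 0.25 and 0.15. Divided by 1 − u: 0.30/0.90 = 33%, 0.25/0.85 = 29%, 0.15/0.75 = 20%. The ordering reverses while the rates of section 8.3 are unchanged.

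**5. Possible distortion, rheumatology vs other.** The spurious difference is the difference in s times t, with t the same in both settings.
- Step 3, c = 0.25: 0.074t, or 0.02, 0.04 and 0.07 SD for t = 0.25, 0.5 and 1. With no true difference, a nominal 5% test at 400:200 would reject in 5.5% to 14% of studies.
- Step 3, c = 0.50: 0.222t, or 0.06, 0.11 and 0.22 SD, with rejection in 10% to 73%.
- Step 4: (0.200 − 0.333)t = −0.133t, the opposite sign.

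The planned effect size for this comparison is 0.281.

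**6. Newly confirmed is not the same as study-prompted.** A rheumatology site completes Module 2 itself and can confirm PsA there, so its share need not arise from the advised consult. If none of it does, the prompted shares in step 4 become 0/29/20% and dermatology sites are the most affected.

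**The case against.** The strongest reply is that no section makes the consult date the diagnosis date. Module 1 records PsA symptoms and diagnosis at the recruiting site, and section 6.1 takes these data from the medical charts. If a recruiting-site date is used, the study creates no date. This stands: it is possible, not stated, that the interval ends at the consult. It does not remove the point, because the pooled analysis then rests on an end date the protocol leaves open for these patients.

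The protocol also presents the consult as routine, guideline-based care that "usually happens between a 12 weeks period after a routine visit at the recruiting site". If that holds for a patient, little delay is removed. But section 4 describes the target population as one "which includes patients with mild disease that are not consulting physicians with rheumatology or dermatology expertise", and for such patients an advised specialist visit is not plainly routine.

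Analysis populations are left to the SAP, which may separate the groups. That is fair, and the absence of derivation detail is not the criticism. The protocol does itself fix the confirmed pool and the linear or logistic models, and neither model accommodates a delay still running at recruitment.

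Short observation after diagnosis affects any recently diagnosed patient. True, but newly confirmed patients are the extreme case and their frequency may vary by specialty.

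A reader might infer that the study shortens the delay most in other sites, by about 0.2 years relative to rheumatology, and so favours those sites. The documents do not support this. The rates in section 8.3 are non-confirmation rates, not suspected shares. The 0.2 years needs 50% confirmation and one year of remaining delay, both assumed (0.333 − 0.111 = 0.22); at 25% confirmation it is 0.07. Shortening is measured against a date nobody observes, and patients who would otherwise have stayed undiagnosed may enter with long delays and raise the mean.

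**Conclusion.** The point holds as a matter of design. Study conduct can supply the confirmation that admits a suspected patient to the primary analysis and may date the end of the first primary endpoint. It leaves almost no time for the two diagnosis-anchored DMARD endpoints, and it operates differently by recruiting specialty. Time from first csDMARD to first bDMARD does not use the diagnosis date and is not affected in this way.

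The net direction, the most affected setting and the size cannot be derived from the protocol. Under equal confirmation rates of 25% to 50%, newly confirmed patients are 3.7% to 11.1% of evaluable patients in rheumatology and 11.1% to 33.3% in other sites. Under an equal 40% suspected share the ordering reverses. The distortions in SD units are illustrations resting on the assumed c, f and t. The study is declared exploratory, which lowers the stakes of any single test but does not make the specialty estimates interpretable if the two groups are mixed.

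**What to change.** - **Data recording form.** Add one item to Module 1: was PsA diagnosed before the recruiting visit, and on what date. Record the date of any confirmation during the study separately. The form itself is not among the documents, so check first whether it already holds this.
- **Section 8.2, DMARD endpoints.** Base time from diagnosis to first csDMARD and to first bDMARD on patients diagnosed before recruitment, including where these times serve as explanatory variables.
- **Section 8.2, onset-to-diagnosis.** Report patients undiagnosed at recruitment separately by specialty, with their delay so far. Analyse the specialty contrast in two ways: with these patients censored at recruitment in a time-to-event model, and with the study-confirmed date. State in advance which is primary.
- **Caveat to state.** If only later-confirmed patients remain eligible, the censored analysis still selects on an event after recruitment. The separate report should therefore also give the number not confirmed, by specialty.

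Cost: one added form item, one time-to-event analysis outside the linear and logistic models now specified, and fewer diagnosis events in the censored analysis. Inclusion criteria, visits and sample size are unchanged. The form item is cheap if added before data collection starts.

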**Figure 1: Study schematic**

[figure not shown]

Confidential Information

No use or disclosure outside AbbVie is permitted without prior written authorization from AbbVie

### **6.1.1. Patient Selection Criteria**

#### **Inclusion criteria**

Patients attending a routine visit at a rheumatologist, dermatologist or non-rheum/non-derm site, who fulfill the following selection criteria, can be included:

- Diagnosed with suspected or established PsA
- Female or male
- Age of 18 years or older
- Signed a patient authorization form to use and disclose personal health information (or informed consent, where applicable)
- Able to read and understand patients questionnaires in provided language

No formal Exclusion criteria exist.

